## Abstract

**Background:**

Care for older adults is facing a number of challenges: health problems are not consistently identified at a timely stage, older adults report a lack of autonomy in their care process, and care systems are often confronted with the need for better coordination between health care professionals. We aim to address these challenges by introducing the geriatric care model, based on the chronic care model, and to evaluate its effects on the quality of life of community-dwelling frail older adults.

**Methods/design:**

In a 2-year stepped-wedge cluster randomised clinical trial with 6-monthly measurements, the chronic care model will be compared with usual care. The trial will be carried out among 35 primary care practices in two regions in the Netherlands. Per region, practices will be randomly allocated to four allocation arms designating the starting point of the intervention. *Participants*: 1200 community-dwelling older adults aged 65 or over and their primary informal caregivers. Primary care physicians will identify frail individuals based on a composite definition of frailty and a polypharmacy criterion. Final inclusion criterion: scoring 3 or more on a disability case-finding tool. *Intervention*: Every 6 months patients will receive a geriatric in-home assessment by a practice nurse, followed by a tailored care plan. Expert teams will manage and train practice nurses. Patients with complex care needs will be reviewed in interdisciplinary consultations. *Evaluation*: We will perform an effect evaluation, an economic evaluation, and a process evaluation. Primary outcome is quality of life as measured with the Short Form-12 questionnaire. Effect analyses will be based on the “intention-to-treat” principle, using multilevel regression analysis. Cost measurements will be administered continually during the study period. A cost-effectiveness analysis and cost-utility analysis will be conducted comparing mean total costs to functional status, care needs and QALYs. We will investigate the level of implementation, barriers and facilitators to successful implementation and the extent to which the intervention manages to achieve the transition necessary to overcome challenges in elderly care.

**Discussion:**

This is one of the first studies assessing the effectiveness, cost-effectiveness and implementation process of the chronic care model for frail community-dwelling older adults.

**Trial registration:**

The Netherlands National Trial Register NTR2160.

## Background

As a result of aging of the population of industrialized countries, the group of community-dwelling older adults with multiple chronic conditions is vastly expanding [1,2]. The subsequent accumulation of complex and long-term health needs causes the demand for care services to increase rapidly, accounting for a considerable share of health care utilization [3]. Globally, usual care is attempting to uphold the standards necessary to deliver high-quality chronic disease care. Pressure on the sustainability of health care systems is likely to further increase in the near future, demanding the identification and targeting of the main bottlenecks in care for frail older adults [4].

In Europe, three major barriers to high-quality care for frail community-dwelling older adults have repeatedly been identified over the past few years. First, our predominantly reactive care system fails to identify many older adults’ health risks and care needs at a timely stage, impeding the successful prevention of adverse outcomes. In addition, older adults experience a lack of autonomy in their own care process. Finally, care for frail older adults living at home is often fragmented, resulting in a lack of coordination and information exchange between health care professionals [5].

Offering integrated chronic care services may be the appropriate approach to overcome the challenges observed in elderly care: Evidence suggests that integrated care models have the potential to successfully improve quality of elderly care and may have a positive effect on health-related outcomes [6]. In addition, qualitative studies evaluating the environmental impact of such models report perceived benefits by informal caregivers [7]. However, overall review findings present a mixed picture, with studies showing inconsistent evaluation outcomes regarding the efficiency and effectiveness of the care models investigated [7-15].

The chronic care model is a multidimensional framework for chronic illness management, designed to guide and enhance the comprehensive and interdisciplinary delivery of care. Previous research has demonstrated its potential to improve health outcomes of patients with a chronic condition, and to improve quality of care [16-19]. Despite the fact that the chronic care model approach is widely used to implement integrated and long-term care services, to our knowledge only one study so far reported using the model to deliver care to community-dwelling frail older persons in a primary care setting [20].

To overcome the aforementioned barriers to high-quality care for older adults, the frail older Adults: Care in Transition (ACT) - study introduces the geriatric care model, a multifaceted intervention based on the chronic care model. Corresponding with the chronic care model, the geriatric care model aims to enable productive interactions between activated, informed patients and proactive, prepared health care professionals by combining in-home geriatric assessments with strong management by expert geriatric teams. To our knowledge, we are the only European study so far to investigate the impact of a chronic care model approach on frail older adults, and to evaluate the effectiveness as well as the cost-effectiveness and implementation process of such an intervention in a stepped wedge cluster randomised clinical trial.

Through implementation of the geriatric care model in a pragmatic trial, we seek to target the untimely recognition of health problems, the lack of autonomy perceived by older adults and the lack of coordination between health care professionals. In doing so, we hope to improve the quality of care for community-dwelling frail older adults, and subsequently improve their quality of life.

## Methods

### Study design and setting

We will implement the geriatric care model using a stepped-wedge cluster randomised clinical trial design. A stepped wedge design is a type of cluster randomized trial design involving sequential roll-out of an intervention to primary care practices (clusters) over a number of time periods [21]. Primary care practices in the control group offer usual care, whereas practices in the intervention group deliver care according to the geriatric care model. By the end of the study, all practices will have started with the intervention. The trial will run over a 24-month period, and will be conducted among a total of 35 primary care practices in the Netherlands, with practices distributed among the regions Amsterdam (18 practices) and West-Friesland (17 practices). The Amsterdam region is of an urban nature, whilst the West- Friesland area can be characterized as an urbanised rural setting. Following participant inclusion, effect measurements will be administered at baseline and at 6, 12, 18, and 24 months (Figure 1). The study received approval by the medical ethics committee of the VU University medical centre. Participants will enrol only after a signed declaration of informed consent.

**Figure 1 F1:**
[figure not shown]
Flow diagram of the ACT-study.

### Randomisation

Per region, primary care practices will be randomised using the computer-based ‘Random Allocation Software’ program. In both regions, primary care practices will be allocated to one of a total of four allocation arms by randomization. The allocation arm number designates the starting moment of the intervention with the geriatric care model at practice level (at 0, 6, 12 and 18 months after baseline). Figure 1 shows the number of primary care practices per region, as well as the starting moment of the geriatric care model on cluster level.

### Study participants and recruitment methods

We will include community-dwelling frail older adults aged 65 years and over, recruited in participating primary care practices involved in the project, and their primary informal caregivers.

Frail older adults will be recruited in three steps.

1. Primary care physicians of participating primary care practices will identify frail individuals based on a composite definition of frailty (experiencing one or more limitations in either physical, psychological and/or social areas) in their population of patients age 65 years and over meeting a polypharmacy criterion: 5 or more drugs prescribed in the last 3 months [22]. Additionally, primary care physicians will include all other older patients meeting the composite description of frailty. Patients are excluded based on the following criteria: Residence outside area of practice registration; residence in a nursing home or in a home for the elderly; cognitive impairment or impaired mental status; critical or terminal illness.

2. Subsequently, all patients included by their primary care physician will receive an information letter and an informed consent form. Within two weeks, individuals selected during step one will be contacted by telephone by a project interviewer and asked to consider study participation.

3. In case of verbal consent, eligibility for trial entry will be established with the Program on Research for Integrating Services for the Maintenance of Autonomy case-finding tool for disability (PRISMA-7) [23]. Eligible patients (score ≥ 3) will be invited to participate in the study, whereupon an appointment will be made for administration of baseline measurements and the collection of the signed informed consent form by a project interviewer.

Primary informal caregivers will be recruited by inquiring with participating older adults. We define a primary informal caregiver as the caregiver carrying most of the care burden for the family member, relative or friend requiring care. If a primary informal caregiver is present, and the participating older adult does not oppose to their involvement in the study, eligible persons will be contacted by telephone and asked to enrol. Informal caregivers interested in participating will receive an information letter and an informed consent form.

### Intervention: geriatric care model

#### Rationale

The geriatric care model aims to target three main challenges care for older adults is currently facing (i.e. untimely detection of older adults’ health risks and care needs, older adults’ lack of autonomy in their care process and inadequate coordination of care). We expect the geriatric care model to improve the quality of the organisation and delivery of care on structure, process and outcome levels. We expect the total impact of this process to improve patient outcomes, resulting in improved self-reported quality of life (Figure 2).

**Figure 2 F2:**
[figure not shown]
Schematic representation of the geriatric care model.

#### Geriatric care model

The geriatric care model aims to enable productive interactions between activated, informed patients and proactive, prepared health care professionals by combining tailored in-home geriatric assessments with strong management. In both the Amsterdam and West-Friesland region, the geriatric care model is integrated into routine practice by an expert geriatric team consisting of an experienced geriatric nurse and an elderly care physician.

#### Geriatric assessments by practice nurses

Every six months, a frail older adult will receive an assessment of health and care needs by a practice nurse, followed by a tailored care plan. This procedure will involve two home visits. During the first visit, a multidimensional assessment will be conducted using the web-based Community Health Assessment version 9.1 of the Resident Assessment Instrument (RAI-CHA) [24]. RAI facilitates the identification of existing care needs, helps nurses standardize their routines, and works as a reminder system for follow-up. After each RAI-assessment, the practice nurse will review the outcomes with the primary care physician and write a tailored care plan. Two weeks after the first visit a second home visit will take place, in which the nurse explores the older adult’s wishes regarding the outcomes of the assessment, provides them with information on appropriate management and/or treatment options, and stimulates their active involvement in the decision making process. According to their nature and content, actions listed in the final care plan will be evaluated by the older adult in consultation with the nurse. At all time, the older adult’s own care wishes will remain at the center of the decision making process.

#### Management by expert geriatric teams

During the intervention the geriatric expert teams will carry out the following three main tasks: (1) (quality) management, (2) expert knowledge transfer and (3) building and maintaining local networks of care organisations (Figure 2).

Management of the quality of care delivery by practice nurses and knowledge transfer will constitute of team meetings, training sessions and multidisciplinary patient reviews. First, team meetings will be held on a regular basis, and if required additional coaching and support will be provided to nurses individually. Additionally, as described in the paragraph below, geriatric team members will organize training sessions conform nurses’ educational needs. The sessions provide a platform for peer supervision and encourage knowledge exchange between nurses. Finally, in the event of a practice nurse reporting a complex patient, a multidisciplinary consultation will be organised by the geriatric team for an interdisciplinary review of the client’s situation. The consultation will be attended by a core group, consisting of the practice nurse, the primary care physician, the pharmacists and the geriatric team members. Depending on the situation demanding the consultation, other health care professionals central to the patient’s treatment (e.g. a physiotherapist) will be invited to join.

Throughout the intervention, the two geriatric teams will set up and maintain regional networks of local organisations. In order to facilitate the coordination between providers of care services for older adults in the region, primary care professionals and representatives of various community-based care organisations will meet on a regular basis, with the aim to subsequently enhance the coordination of care on a patient level.

#### Education of professionals

Practice nurses carrying out the intervention will take part in a tailored training program. Prior to the start of the intervention, nurses will participate in a 3-day motivational interviewing course. Further, both the practice nurses and the geriatric team members will participate in a one day RAI workshop before carrying out the intervention. In order to prevent contamination bias between the allocation arms, nurses will start their training program shortly before they start working with the geriatric care model. Alongside the intervention a second training program will run, consisting of a ‘training on the job’ motivational interviewing session as well as clinical education on geriatric topics provided by the expert team staff. Expert team members will identify each session’s topic(s) by means of field observations and RAI-output reviews. Several months into the intervention, practice nurses and the geriatric team members will be offered a refresher course RAI.

#### Strategies for implementation

Implementation of the geriatric care model is predicated upon the idea of the professional self-regulation of expert teams and practice nurses. Before the intervention is carried out its main theoretical and practical content is outlined by the research team, where after the development of work routines and protocols is informed by the professionals’ experiences in the field without research staff interference.

To avoid contamination, nurses working with the geriatric care model will not be employed in primary care practices in the control group that have yet to start delivering the intervention.

### Control group: usual care

Aimed at providing integral care services, primary care in the Netherlands plays an important role in the organisation of community elderly care. Of people over 75, almost hundred percent initiate contact with a primary care physician at least once a year [25]. Offering both (sub)acute and chronic care to older adults living at home, primary care physicians work in close collaboration with local health care services. A primary care physician may refer an older adult to a variety of local care organisations, whose services range from specialised in-home care to mental health support.

### Evaluating the geriatric care model

We will perform an effect evaluation, an economic evaluation, and a process evaluation. Throughout the 2-year data collection period older adults will advice researchers on the appropriateness and quality of the content of qualitative and quantitative research material, and will assist researchers with the interpretation of qualitative data derived from interviews with older adults.

### Effect evaluation

The primary outcome of the study is quality of life as measured by the 12-item Short Form questionnaire (SF-12) [26]. The SF-12 measures quality of life in two domains: a mental health component score (MCS) and a physical health component score (PCS). All outcome measures are presented in Table 1.

**Table 1 T1:** Overview of outcomes, baseline measurements and follow-up measurements

**Older adults**		**Instrument**	**Baseline**	**6 Months**	**12 Months**	**18 Months**	**24 Months**
**Patient outcomes**	1. Quality of Life	SF-12 [26]	**x**	**x**	**x**	**x**	**x**
	2. Health-related Quality of Life	EuroQol (EQ-5D) [27]	**x**	**x**	**x**	**x**	**x**
	3. Independence in ADL	Katz ADL index [28]	**x**	**x**	**x**	**x**	**x**
	4. Psychological Wellbeing	RAND-36 subscale [29]	**x**	**x**	**x**	**x**	**x**
	5. Social Functioning	1 item on RAND-36 scale	**x**	**x**	**x**	**x**	**x**
	6. Self-reported Health	2 items on RAND-36 scale	**x**	**x**	**x**	**x**	**x**
	7. Acute Hospital Admissions	1 item of our data set and Cost Dairies	**x**	**x**	**x**	**x**	**x**
**Quality of Care**	8. Care Needs	CANE [30]	**x**		**x**		**x**
**Process Outcomes: Achieved transition**	9. Patient-reported Client-centred Care	CCCQ [31]	**x**	**x**	**x**	**x**	**x**
	10. Coordination of Care from the patient’s perspective	2 items on QUOTE [32]	**x**	**x**	**x**	**x**	**x**
**Informal Caregivers**		**Instrument**	**Baseline**	**6 Months**	**12 Months**	**18 Months**	**24 Months**
**Carer outcomes**	12. Quality of life	SF-12	**x**	**x**	**x**	**x**	**x**
	13. Self-rated Burden of Care	CarerQol [33]	**x**	**x**	**x**	**x**	**x**
**Older adults and informal caregivers**		**Instrument**	**Baseline**	**6 Months**	**12 Months**	**18 Months**	**24 Months**
**Costs**	Direct and Indirect Costs	Cost diaries					

*SF-12* Short Form-12 questionnaire; *EuroQol (EQ-5D)* measures of 5 dimensions of health-related quality of life; *Katz ADL* Katz Activities of Daily Living; *RAND-36* measure of health-related quality of life; *CANE* Camberwell assessment of needs in the elderly; *Arm 1-4* allocation arm number 1–4; *CCCQ* Client-centred Care Questionnaire; *QUOTE* QUality Of care Through the patient’s Eyes; *CarerQol* care-related quality of life of informal caregivers

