#### Sample size calculations

Sample size calculations are based on the expected effects of the intervention on the primary outcome, quality of life, measured by the SF-12. Calculations are done using the equation for a longitudinal design [34] and adjusted for the effect of clustering of primary care practices [35]; SF-12 coefficients used in the calculations are derived from previous studies with a study population similar to ours. The number of follow up measurements is 4; Mean cluster size is based on the expected number of participants per cluster at baseline (N = 33). We assume the following: a standard deviation of 7.1 (PCS and 6.6 (MCS) [36], a correlation coefficient of repeated measurements of 0.66 (PCS) and 0.5 (MCS) [37], an intra-cluster correlation coefficient of 0.02 for both PCS and MCS [36], an alpha of 0.05 and a power of 90%. To detect a clinical difference of 3 points [29] on the SF-12 scale between intervention and control groups and assuming an attrition rate of 20%, the study would require 180 (PCS) and 131 (MCS) eligible patients per arm.

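### The one named primary outcome is two SF-12 component scores, each sized at a full alpha of 0.05, with no rule for what counts as success

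*Protocol article*

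**What the plan says.** The abstract treats the primary outcome as one quantity: "Primary outcome is quality of life as measured with the Short Form-12 questionnaire". The Effect evaluation section repeats this ("The primary outcome of the study is quality of life as measured by the 12-item Short Form questionnaire (SF-12")) and immediately adds: "The SF-12 measures quality of life in two domains: a mental health component score (MCS) and a physical health component score (PCS"). It defines no combined score and does not put one component ahead of the other.

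The section on sample size calculations handles the components separately. Each has its own standard deviation and its own correlation between repeated measurements. A single error specification serves both: "an alpha of 0.05 and a power of 90" percent. The result is two requirements, 180 per arm for PCS and 131 per arm for MCS.

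The Analyses section says that every outcome measure will be compared between care model and usual care by multilevel regression. It gives no test level, no order of testing and no criterion for a positive primary result.

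**The concern.** A trial with one primary outcome needs one primary test, or a rule that links several. Here one label covers two scores, and each score is planned as though it had the whole 5% to itself. Without a rule, three readings remain open: either score suffices, both must succeed, or one is the real primary outcome and the other supports it. They differ in error rate and in power, and the choice could be made after the results are known.

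This matters more than usual here. The Blinding section says that participants and interviewers will know the group assignment, and the outcome is self-reported. A success rule set in advance is one of the few protections left for the main claim.

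**Working it through.** **Inputs, all from the sample size section.** Standard deviations: "a standard deviation of 7.1 (PCS and 6.6 (MCS"). Repeated-measures correlations: "a correlation coefficient of repeated measurements of 0.66 (PCS) and 0.5 (MCS"). Follow-ups: "The number of follow up measurements is 4". Clustering: "an intra-cluster correlation coefficient of 0.02 for both PCS and MCS", with a mean cluster size of 33. Target difference 3 points, attrition 20%, power 90%.

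**Step 1. Reproduce the plan's figures.** The formula is n = 2 × (z₁ + z₂)² × SD² / 3² × [1 + (4 − 1)ρ] / 4. The result is multiplied by the design effect 1 + (33 − 1) × 0.02 = 1.64 and divided by 0.80 for attrition.

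| Alpha per score | PCS per arm | MCS per arm | Matches 180 / 131? |
|---|---|---|---|
| 0.05 two-sided | 87.69 × 1.64 / 0.8 = 179.8 | 63.57 × 1.64 / 0.8 = 130.3 | yes |
| 0.05 one-sided | 146.5 | 106.2 | no |
| 0.025 two-sided (split) | 103.58 × 1.64 / 0.8 = 212.3 | 75.09 × 1.64 / 0.8 = 153.9 | no |

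The article does not state whether alpha is one- or two-sided. Of these three versions only the two-sided, undivided 0.05 gives the printed numbers, so no allowance for two scores is built into the sizing.

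**Step 2. Error rate if either score suffices.** Under independence it is 1 − 0.95² = 0.0975. The article gives no correlation between the PCS and MCS tests, so the table uses assumed values and a bivariate normal calculation with neither score truly affected.

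| Assumed test correlation | Either score significant, any direction | Either score significant in favour of the care model | Both scores significant, two-sided |
|---|---|---|---|
| 0 | 9.75% | 4.94% | 0.25% |
| 0.3 | 9.51% | 4.76% | 0.49% |
| 0.5 | 9.07% | 4.54% | 0.93% |
| 0.7 | 8.35% | 4.17% | 1.65% |
| 0.9 | 7.04% | 3.52% | 2.96% |

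The benchmark for the second column is 5%. For the third it is 2.5%, the favourable half of one two-sided 0.05 test.

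**Step 3. If both scores are required.** The error cannot exceed 5%, because each score alone must pass at 0.05. Power is what changes. With each score at its own 90%, joint power is 0.90 × 0.90 = 0.81 if the tests are independent, and cannot fall below 1 − 0.10 − 0.10 = 0.80. If 180 per arm is used for both scores, MCS power is Φ(3.2415 × √(180 / 130.32) − 1.96) = Φ(1.85) = 0.968. Joint power is then about 0.90 × 0.968 = 0.87 under independence.

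**Step 4. Cost of splitting alpha.** At 0.025 per score the requirement rounds up to 213 (PCS) and 154 (MCS). At the stated 180 and 131, power per score would fall from 90% to about 84%. The abstract plans 1200 participants, or 1200 / 4 = 300 per allocation arm if arms are equal. By the same formula, 300 per arm gives 97.4% (PCS) and 99.6% (MCS) at 0.025, against 98.7% and 99.8% at 0.05.

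**The case against.** **The either-score rule is not in the text.** This is correct. A reader might infer that the trial carries a false positive rate of nearly 10%, but the article does not support that as a fact. It does not say that one significant score is enough, and separate sizing is equally consistent with requiring both. The figure is an upper value under one possible rule and near-independent tests.

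**The 9.75% counts findings of harm.** Also correct. For a claim that the care model improves quality of life, the relevant range is 3.5% to 4.9%. Set against its proper benchmark of 2.5%, this is still an inflation, close to a doubling when the tests are independent.

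**The 0.05 is a sizing input.** The Analyses section gives no test level, so the level for the final tests is inferred from the sizing.

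**The rule may sit in the statistical analysis plan or full protocol.** Multiplicity procedures often do, and their absence from an article would not by itself be a finding. What stands is narrower. Whether the primary outcome is one quantity or two belongs to its definition, and the article fixes two calculations at full alpha under one label. A later document that split alpha would no longer agree with 180 and 131. One that required both scores would change what the 90% refers to. Under either rule the published sizing statement would need rewording.

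**Conclusion.** The point holds in conditional form. The article defines one primary outcome, plans it as two tests each at an undivided 0.05, and states no ranking, success rule or adjustment. The absence of a split is shown by the exact reproduction of 180 and 131.

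The size of the problem depends on a rule the article does not give. If either score suffices, the two-sided familywise error lies between 7.0% and 9.75% over assumed correlations from 0.9 to 0, and false claims of benefit between 3.5% and 4.9% against 2.5%. If both are needed, error is controlled and the weakness is that 90% is not the power for success. The article does not allow a choice between these readings, so no single inflated error rate can be attributed to the trial. It should be settled before analysis, and the remedy needs no change to the planned enrolment.

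**What to change.** Declare PCS and MCS as two primary outcomes and test them with the Holm procedure at a familywise two-sided 0.05: the smaller p-value against 0.025 and, if that succeeds, the larger against 0.05. Restate the sample size at alpha 0.025 as 213 (PCS) and 154 (MCS) per arm, and state that alpha is two-sided.

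The cost is a sentence in the outcome section and revised figures in the sample size section. No extra patients are needed if about 300 per arm are enrolled. By the plan's own formula, power at the stricter level remains 97% and 99.6%, a small loss of sensitivity per score.

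Other explicit rules would also close the gap: naming one score as primary, testing in a fixed order, or requiring both. If both are required, the power statement should give joint power. At 300 per arm this is about 0.987 × 0.998 = 0.985 under independence, by the same formula.
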